## Description of protocol

### Overview

This protocol employs a laboratory-based, randomized within-subject crossover experimental design to examine the associations between contagious yawning stimuli exposure and subjective and physiological indicators of sleepiness. The protocol follows a 2 × 2 factorial structure manipulating: (1) stimulus type (human vs. digital character yawning) and (2) auditory content (with vs. without sound), yielding four experimental conditions.

Participants complete two sessions on separate days. In one session, they view human yawning videos under both auditory conditions in randomized order. In the other session, they view yawning videos of digital characters under the same auditory conditions. The order of sessions (human first vs. digital first) will be counterbalanced across participants. The order of conditions will be randomized and counterbalanced to minimize systematic order effects.

A within-subject design was selected to maximize sensitivity to condition-related differences while controlling for interindividual variability in baseline sleepiness, circadian preference, and autonomic functioning. To mitigate potential fatigue or habituation effects, experimental sessions will be conducted on separate days with a minimum interval of one-day between sessions.

The protocol is designed to examine relative differences across yawning stimulus conditions and within-subject changes over time, rather than to isolate yawning-specific causal effects relative to neutral stimulus exposure. Accordingly, non-yawning control conditions are not included. This design enables focused comparison across stimulus modalities and representations while maintaining a manageable experimental duration within a multimodal physiological recording context, which is consistent with prior studies using contagious yawning stimuli [26,27]. Pre-stimulus baseline recordings will be obtained prior to each condition, which allows within-subject quantification of changes relative to a stable resting reference.

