Finally, a video camera will be positioned to capture the participant’s facial expressions throughout the session. The camera angle will be adjusted to ensure a clear view of the face, and ambient lighting will be optimized to support subsequent behavioral coding. A brief test recording will be conducted to confirm that facial features are clearly visible.

To ensure consistency across participants, the experimental environment will be standardized. Room temperature will be maintained between 20 and 22 °C throughout the session. Lighting conditions will be controlled at a moderate and consistent level. External noise and potential interruptions will be minimized as much as possible. Participants will be seated comfortably in a chair with back support, and the display screen will be positioned at eye level and at an appropriate viewing distance to reduce physical strain.

Following equipment setup, a five-minute baseline physiological recording will be conducted. This duration was selected based on prior studies examining the signal lengths required to reliably derive downstream physiological and cognitive indices [[37], [38], [39]]. Participants will be instructed to sit quietly in a reclining chair and relax while maintaining their gaze on a neutral fixation point displayed on the screen. All physiological signals will be recorded continuously during this period. To avoid introducing confounding influences, no conversation or additional instructions will be provided during the baseline recording.

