#### Data pre-processing

Physiological and behavioral data will be time-aligned across sensing modalities using synchronized timestamps. For each yawning condition, physiological signals will be segmented into predefined analysis windows relative to stimulus onset.

Artifact removal will then be performed separately for each sensing modality. For wristband-based signals, visual inspection and accelerometer data will be used to identify motion artifacts, signal dropout, and periods of excessive movement, which will be excluded from further analysis. For eye-tracking data, periods of sustained eye closure indicative of potential sleep onset as well as poor-quality pupil measurements, will be excluded. For fNIRS data, standard preprocessing procedures including bandpass filtering and motion artifact correction will be applied, followed by the removal of segments affected by low signal quality. Raw optical signals will subsequently be converted into HbO_2_ and HHb concentration changes.

To ensure that analyses capture stimulus-related physiological responses rather than transitions into sleep, only data recorded prior to identified sleep onset will be included in confirmatory analyses. Data segments affected by excessive artifacts, signal loss, or sustained eye closure will be excluded from primary analyses. Baseline correction will be applied to all physiological measures to account for inter-individual differences in resting physiological states. Baseline values will be calculated for each participant using pre-stimulus periods and subtracted from condition-specific values or expressed as percentage changes, as appropriate.

Following signal cleaning, physiological features will be extracted for each experimental condition. BVP will be used to compute mean heart rate and HRV metrics, including SDNN, RMSSD, and frequency-domain measures. EDA data will be analyzed to derive tonic skin conductance level and phasic skin conductance responses. Pupil data will be used to calculate mean pupil diameter, pupil diameter variability and pupillary unrest index (PUI). Skin temperature data will be summarized using mean peripheral temperature and changes relative to baseline. For fNIRS data, temporal patterns of cortical oxygenation changes will be extracted. Finally, descriptive statistics will be used to summarize participant characteristics, baseline sleep measures, and data completeness.

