#### Data analysis

The protocol is designed to examine relative differences across yawning stimulus conditions and within-subject changes over time, rather than to establish yawning-specific causal effects relative to neutral stimulus exposure. As such, findings will be interpreted in terms of associations with yawning stimulus exposure and relative differences across conditions, rather than as evidence of yawning-specific causal effects.

The primary outcome will be the change in subjective sleepiness, as assessed using post-condition KSS ratings. Analyses will focus on within-subject changes in KSS across experimental conditions, as well as changes relative to baseline measurements.

Secondary outcomes will include physiological markers associated with sleepiness and arousal, including autonomic nervous system activity (e.g., HRV, EDA), skin temperature variation, pupil size dynamics, and neural activity patterns associated with reduced alertness. These measures are selected based on prior literature demonstrating their sensitivity to changes in vigilance and alertness. For example, HRV has been shown to increase with sleepiness and reduced vigilance, often reflecting shifts toward parasympathetic dominance, particularly in low-frequency bands [45,46]. Similarly, pupillary measures such as the PUI have also been associated with increased sleepiness and reduced alertness [47,48]. In addition, decreases in oxygenated and total hemoglobin in prefrontal regions, as measured by fNIRS, have been linked to fatigue and reduced alertness [49].

While these physiological measures have been widely used as indices of arousal and vigilance, they are not universally established as direct measures of subjective sleepiness. Accordingly, these measures will be interpreted as complementary indicators of arousal-related processes in conjunction with subjective and behavioral measures. Analytical focus will therefore be placed on changes in physiological signals relative to baseline and on their associations with subjective sleepiness, rather than attempting to derive a single direct physiological measure of sleepiness.

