Exploratory outcomes will include behavioral indicators of sleepiness, such as yawning occurrence and instances of sleep onset observed during the experiment. Additional exploratory analyses will examine the relationship between yawning behavior and both subjective and physiological outcomes. These relationships will be modeled using mixed-effect approaches where appropriate, which allows for the inclusion of both within-subjects (e.g., condition, time) and between-subjects (e.g., chronotype, baseline sleep quality) factors.

Statistical significance will be evaluated using two-sided tests with an alpha level of 0.05 unless otherwise specified. Results will be reported using effect sizes (e.g., estimated mean differences as quantified by Cohen’s *d* or Hedge’s *g*) alongside 95% confidence intervals and p-values. Given the exploratory nature of several outcomes, findings will be interpreted with appropriate caution, and emphasis will be placed on the direction, magnitude, and consistency of observed effects rather than statistical significance alone. The data analysis plan is summarized in Table 2.

**Table 2 tbl0002:** Data analysis plan.

Analysis Level	Procedure
Primary outcome analysis	▪ Analyze changes in KSS using linear mixed-effects models to account for the within-subject repeated-measures design ▪ Fixed effects will include stimulus type (human vs digital character yawning), auditory condition (with sound vs without sound), and their interaction. ▪ Subject will be included as a random effect with a random intercept to account for interindividual differences in baseline sleepiness. ▪ Where model convergence permits, random slopes for condition effects may be explored. ▪ Conduct planned comparison [50] to examine differences in subjective sleepiness between human and digital yawning stimuli, differences between auditory conditions (with vs without sound), and the interaction between stimulus type and auditory condition.
Secondary outcome analysis	▪ Apply the mixed-effects modeling framework used for primary outcome analysis to each physiological outcome, including HRV, EDA, skin temperature, pupil dynamics, and fNIRS measures. ▪ Analyses will focus on changes relative to baseline and associations with experimental conditions. ▪ Where appropriate, multiple comparison adjustments (e.g., Bonferroni or false discovery rate correction) will be reported as supplementary information.

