Exploratory analysis	▪ Examine sleep onset occurrence and sleep onset latency based on behavioral and physiological indicators. ▪ Count observable yawning events by condition. ▪ Examine the relationship between yawning frequency and outcome measures (KSS scores and physiological measures) using mixed-effect models. ▪ Where temporal resolution permits, conduct event-based analyses to examine short-term physiological responses surrounding yawning events. ▪ Explore moderation effects by including interaction terms in mixed-effects models (e.g., chronotype, habitual sleep quality, baseline sleepiness, and personality traits).
Model diagnostics	▪ Inspect Q-Q plots of residuals to assess normality. ▪ Plot residuals vs fitted values to check homoscedasticity. ▪ Use formal diagnostic tests where appropriate (Shapiro-Wilk, Breusch-Pagan). ▪ Report any violations and their potential impact on inference and apply transformations if necessary.

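### Percentage change from baseline, which the protocol permits for any physiological measure, has a mean above zero when nothing changed; a log-ratio would avoid this for the variable, positive features

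*Protocol article*

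**What the plan says.** The Data pre-processing section of the protocol article sets the scope: "Baseline correction will be applied to all physiological measures to account for inter-individual differences in resting physiological states". It then names two forms of correction: "Baseline values will be calculated for each participant using pre-stimulus periods and subtracted from condition-specific values or expressed as percentage changes, as appropriate". No feature is assigned to either form, and a log-ratio is not offered.

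The denominator of any percentage is a short resting record. The Equipment and environment setup section says that "a five-minute baseline physiological recording will be conducted", and the Overview says that "Pre-stimulus baseline recordings will be obtained prior to each condition". Artefact exclusion may shorten the usable record further.

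For the secondary outcomes, Table 2 applies the KSS mixed model (stimulus type, sound, interaction) and adds: "Analyses will focus on changes relative to baseline and associations with experimental conditions". The Data analysis text also puts its analytical focus on physiological change from baseline. It gives a direction for one marker: "HRV has been shown to increase with sleepiness and reduced vigilance, often reflecting shifts toward parasympathetic dominance". PUI is described only as associated with greater sleepiness. The model-diagnostics row of Table 2 ends: "Report any violations and their potential impact on inference and apply transformations if necessary". The Overview states that there is no non-yawning control.

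**The concern.** A percentage change divides by one noisy resting value. A baseline that is low by chance inflates the ratio by more than an equally high one deflates it, so the average of the individual percentages is pulled upward.

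Two illustrative records show it. One person has RMSSD 30 at rest and 40 during the film (+33.3%). Another has 40 at rest and 30 during the film (−25.0%). The mean RMSSD is 35 in both windows, so nothing changed on average, yet the mean percentage change is (33.3 − 25.0)/2 = +4.2%.

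The first research question asks whether human yawning videos go with sleepiness-related responses. Without a neutral film, its physiological answer rests on change from baseline. An upward artefact in HRV would then read as support. The artefact grows with measurement noise, so noisier features would show larger apparent percentage changes. That matters in a plan that emphasises the direction, size and consistency of effects. The residual plots in Table 2 may show skewness, but they do not reveal a shifted mean.

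**Working it through.** The protocol article states no sample size and no within-person variability, so there is no figure of its own to reproduce.

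**Inputs from the document.** Percentage change is allowed for each participant. Change from baseline is a focus. Tests are two-sided at 0.05. The four conditions fall in two sessions.

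**Assumptions.** With no effect, baseline B and film value X for a person are log-normal with the same log-mean, the same log-SD s and correlation ρ between windows. s, ρ and N = 40 are all assumed.

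**Bias.** ln(X/B) is normal with mean 0 and variance 2s²(1−ρ). Hence E[X/B] − 1 = exp(s²(1−ρ)) − 1, while E[X − B] = 0 and E[ln(X/B)] = 0.

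| s | ρ = 0 | ρ = 0.5 |
|---|---|---|
| 0.05 | exp(0.0025) − 1 = 0.25% | exp(0.00125) − 1 = 0.13% |
| 0.25 | exp(0.0625) − 1 = 6.4% | exp(0.03125) − 1 = 3.2% |
| 0.35 | exp(0.1225) − 1 = 13.0% | exp(0.06125) − 1 = 6.3% |
| 0.50 | exp(0.25) − 1 = 28.4% | exp(0.125) − 1 = 13.3% |

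**As a standardised effect.** With ρ = 0 and one condition, the standard deviation of X/B is exp(s²)·√(exp(2s²) − 1). The spurious d is 0.0645/0.388 ≈ 0.17 at s = 0.25 and 0.284/1.034 ≈ 0.27 at s = 0.50.

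**Testing the mean change against zero.** These are simulated null trials with N = 40 and the four conditions averaged. One-sample t-tests stand in for the mixed-model intercept. With one baseline per session, the rejection rates are:

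| s | percentage, ρ = 0 | percentage, ρ = 0.5 | log-ratio |
|---|---|---|---|
| 0.25 | about 38% | about 21% | about 5% |
| 0.35 | about 62% | about 37% | about 5% |
| 0.50 | about 88% | about 63% | about 5% |

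Nearly all rejections on the percentage scale are upward. A separate baseline for each condition, as the Overview can be read, raises the rates: at s = 0.3, ρ = 0 and N = 40, from about 50% to about 69%. For a single condition with ρ = 0 they are lower: about 14%, 22% and 36% at s = 0.25, 0.35 and 0.50.

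**The planned contrasts.** In the same null settings on the percentage scale, human vs digital, sound vs silent and their interaction reject in about 4% to 6% of trials, because a bias common to all conditions subtracts out. It would enter a contrast only if noise differed by condition. For example, log-SD 0.3 in one condition and 0.2 in another, with ρ = 0, gives exp(0.09) − exp(0.04) = 1.094 − 1.041 = 5.3 percentage points.

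**The case against.** **The scale for each feature belongs in an analysis plan, and a condensed article may leave it out.** That would dispose of a complaint about missing detail. It does not dispose of this one: the article names the forms it allows, one of them is biased for these features, and the log-ratio is not among them.

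**Percentage change is permitted, not assigned.** This stands. Nothing says that HRV, PUI or fNIRS will be expressed as a percentage, and subtraction is named first. The point concerns an option left open, not a calculation that is certain to be made.

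**A reader might infer that the main secondary tests carry large false-positive rates.** The document does not support that. Table 2 plans comparisons between conditions, and those keep about 5% error. The inflated rates belong to testing mean change against zero. Table 2 does not list that as a planned comparison, although the stated focus and the first research question call for that reading.

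**A reader might infer that neither form of correction works.** That does not hold. Subtraction has no bias under no change. A log cannot be taken of a change score that fell, but Table 2 does not say that the change score is what would be transformed.

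**The size rests on assumed inputs.** This stands. Independent noise in two windows of one session is the least favourable case shown; ρ = 0.5 about halves the bias.

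**Interpretation is already restrained.** The Data analysis section treats these measures as complementary indicators, and the Limitations section concedes time-on-task, fatigue and repeated exposure. An artefact of the calculation would arise without any of these, so the concession does not cover it. The upward direction is explicit for HRV and only inferred for PUI.

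**Conclusion.** The point holds within limits. If percentage change is used for SDNN, RMSSD, band power, skin conductance level or PUI, the mean change from baseline is biased upward under no effect by exp(s²(1−ρ)) − 1. Over the assumed range s = 0.25 to 0.50, that is about 6% to 28% with ρ = 0 and about 3% to 13% with ρ = 0.5. Whether these features lie in that range is an assumption. For a feature with s near 0.05 the bias is negligible.

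The exposure is confined to change-from-baseline readings of secondary outcomes, chiefly the physiological part of the first research question. The contrasts between conditions are protected as long as noise is similar across conditions, and the KSS primary outcome is untouched. A blanket ban on percentages for pupil diameter or skin temperature would be a preference and is not part of this point. For HbO₂ and HHb, which are already concentration changes, a percentage could divide by a value near zero; the protocol does not say that it will be used there. This is a cheap improvement, not a flaw in the main comparisons.

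**What to change.** In Data pre-processing, drop the percentage option for SDNN, RMSSD, HRV band power, skin conductance level and PUI. For these, analyse ln(film) − ln(baseline) and report exp(estimate) − 1 as the percentage change in geometric mean. State that HbO₂ and HHb are corrected by plain difference. In the model-diagnostics row of Table 2, add that any transformation is applied to the raw feature before baseline correction.

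The cost is one or two sentences and no new data. The downside is that results become ratios of geometric means, and a feature with true zeros, such as a count of phasic skin conductance responses, needs a plain difference or a count model.

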### Yawning stimulus materials

Human yawning stimuli will be compiled from publicly available video recordings, drawing on sources such as YouTube (the “yawn-o-meter”), TikTok, and the YawnStim dataset [43]. Clips will be selected based on clear visibility of facial expressions and the presence of naturalistic yawning behavior. Each condition will include approximately 50 discrete, non-repeating yawning events, each lasting 6 s [41,42], resulting in a total stimulus duration of 5 min. The final stimulus set will include a balanced representation of male and female individuals.

Digital character yawning stimuli will be generated using generative AI tools to produce controlled yet diverse animated yawning clips. Stylized animal-like characters (e.g., cats and dogs) will be used to reduce potential confounds associated with human identity, attractiveness, or familiarity, while preserving clearly recognizable yawning behavior. Animal-like characters were selected because they are sufficiently human-dissimilar to avoid uncanny valley effects, yet sufficiently familiar to elicit socially contagious responses, consistent with prior evidence that contagious yawning occurs across species [44]. Each clip will be structured to reflect the typical temporal phases of a yawn, including gradual mouth opening, peak extension, and closure, with smooth motion transitions. Slight variations in timing and motion will be introduced to maintain naturalness while avoiding repetition. All generated clips will undergo manual selection and standardization to ensure experimental consistency. Clips with ambiguous expressions, unnatural motion, or technical artifacts will be excluded. Remaining clips will be standardized in duration, resolution, and presentation format.

For audiovisual conditions, yawning sounds will be synchronized with the peak mouth-opening phase of each clip, while silent conditions will use identical clips without audio. For the human yawning clips with audio, the original audio from the source clips will be retained. For digital pet clips and human yawning clips without audio, yawning sounds will be synthesized using audio generation tools. Generated sounds will be standardized in amplitude and duration and evaluated for perceived naturalness prior to use. Stimulus sequences will be matched across human and digital pet conditions in terms of the number of yawns, inter-yawn intervals, and total duration.

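### Pupil change from baseline compares a film of changing clips with a static fixation screen, so the unrest index and pupil variability can move without any change in alertness

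*Protocol article*

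**What the plan says.** **Baseline.** Under Equipment and environment setup, "a five-minute baseline physiological recording will be conducted", with participants "maintaining their gaze on a neutral fixation point displayed on the screen". The Overview says that such a baseline precedes each condition and treats it as the resting reference. Room lighting is held constant.

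**Film.** Under Yawning stimulus materials, "Each condition will include approximately 50 discrete, non-repeating yawning events, each lasting 6 s", "resulting in a total stimulus duration of 5 min". "Human yawning stimuli will be compiled from publicly available video recordings", from several kinds of source, and the digital clips are generated. The generated clips are standardized for length, resolution and format. The human and digital sequences are matched on the number of yawns, their spacing and total length. Screen luminance and contrast are on neither list.

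**Processing.** Data pre-processing lists the pupil features: "Pupil data will be used to calculate mean pupil diameter, pupil diameter variability and pupillary unrest index (PUI". Cleaning removes sustained eye closure and poor-quality samples. Every physiological measure is then baseline-corrected, by subtraction or as a percentage change.

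**Interpretation.** Data analysis cites the unrest index as a correlate of sleepiness and continues: "Analytical focus will therefore be placed on changes in physiological signals relative to baseline and on their associations with subjective sleepiness". Table 2 repeats the focus on change from baseline for the secondary outcomes, pupil dynamics included.

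**The concern.** The unrest index and pupil variability accumulate pupil movement whatever its cause. They can stand for sleepiness only if the visual input is the same in the two periods compared. Here one period is a constant screen and the other a sequence of different scenes. Movement evoked by the scenes is counted as unrest, in the direction that the article associates with sleepiness, and subtracting the fixation value leaves it in the outcome.

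What is at stake is research question 1 (Background), whether human yawning videos are associated with sleepiness-related responses. With no neutral film in the design, the pupil evidence on that question is film minus baseline. The article also says that it will weigh the direction and consistency of effects. A visual effect shared by all four conditions would give just such a consistent pattern and could pass for corroboration of the sleepiness ratings.

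**Working it through.** **The article's own figure.** 50 clips × 6 s = 300 s = 5 min, as stated. The clips therefore fill the film back to back, with 50 − 1 = 49 clip changes, one every 6 s (1/6 ≈ 0.17 Hz). The fixation screen has none.

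**Structure.** Write the film value as F = B + A + S, where B is the fixation value, A the effect of the changed visual input and S any true change in state.
- Change from baseline: F − B = A + S. A stays in.
- Human minus digital: (A_h − A_d) + (S_h − S_d). A cancels only if it is equal in the two films.
- Sound minus silent: A cancels, because the silent conditions use the same clips.

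**Simulation, alertness held constant (S = 0).** The documents give no pupil amplitude, screen brightness or formula for the index, so all of the following are assumptions. Traces last 300 s at 25 Hz. The index is Σ|m(k+1) − m(k)| / 5 min, with m(k) the means of successive 0.64-s windows. Spontaneous fluctuation is autoregressive with a 1-s time constant and the same SD in both periods. The film adds a different pupil level per clip (SD given below), a brief constriction at each clip change (size given below), or both. Entries are the ratio of film to fixation index.

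| Response to clips (mm) | Spontaneous SD 0.05 mm | 0.10 mm | 0.20 mm |
|---|---|---|---|
| None | 0.99 | 1.00 | 1.01 |
| Constriction 0.1 | 1.26 | 1.08 | 1.03 |
| Constriction 0.2 | 1.76 | 1.26 | 1.07 |
| Level SD 0.1 | 1.19 | 1.06 | 1.03 |
| Level SD 0.2 | 1.51 | 1.21 | 1.06 |
| Level SD 0.2 + constriction 0.2 | 2.00 | 1.36 | 1.11 |
| Level SD 0.4 + constriction 0.2 | 2.59 | 1.68 | 1.23 |

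With some response to the clips, the rise runs from 3% to 159%. With none, there is no rise.

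**Four films with the same clip variation** (spontaneous SD 0.10 mm, level SD 0.2 mm, constriction 0.1 mm). Mean change from baseline was +1.31 mm/min (SD 0.25) and the human-digital contrast averaged −0.01 (SD 0.28). Against a fixation value of about 5.5 mm/min, 1.31 / 5.5 ≈ 24%.

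**Relaxing equal fluctuation.** This variant uses a 1.5-s time constant for the fluctuation, level differences only (smoothed over 0.5 s), and spontaneous SD 20% lower during the film.
- Fixation SD 0.10 mm: −11% at level SD 0.1 mm and +7% at 0.2 mm.
- Fixation SD 0.06 mm: about 0% and +35%.

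The net sign is therefore not fixed.

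**The case against.** The strongest reply has four parts.

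1. *The fixed effects in Table 2 are stimulus type, sound and their interaction.* A shift common to all films goes into the intercept and leaves these contrasts alone. This stands. A reader might infer that the planned human-digital and sound tests are invalid, but the documents do not support that. The sound contrast is protected. The human-digital contrast is exposed only so far as the two films differ in luminance and its variation, and matching on these is not stated.

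2. *The article is cautious.* It calls the physiological measures complementary rather than direct, disclaims yawning-specific causal effects and admits that it has no neutral condition. This softens the interpretation but does not cover the point. Those caveats concern what a real change of state may be attributed to, whereas here the index can move with no change of state. The limitations give time-on-task, fatigue and repeated exposure as examples and do not mention visual input.

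3. *The size and sign rest on assumptions.* This also stands. A reader might infer that every condition must show a raised index by construction. That needs equal spontaneous fluctuation at fixation and during the film, and a film may engage viewers more than sitting quietly does. Nor do the documents show a rise if brightness were equalised across clips. Some effect would then remain only if the pupil also responds to content or to the clip change itself.

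4. *The algorithm and any luminance correction may sit in a fuller document.* They may. The point does not rest on their absence: the article itself fixes the fixation baseline, the changing film, the subtraction and the focus on change from baseline.

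**Conclusion.** The concern holds for pupil change from baseline. The unrest index and pupil variability can rise from fixation to film with alertness unchanged, in the direction that the article links to sleepiness. The rise in the index is about 3% to 160% under the assumed amplitudes and equal spontaneous fluctuation. It is smaller, or negative, if that fluctuation falls during the film. For mean diameter the comparison is confounded too, but its direction is undetermined because neither film nor fixation-screen brightness is given.

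The reach is limited: this is a secondary marker, and what suffers is the pupil evidence for research question 1. A reader might also infer that the planned association with the sleepiness ratings is weakened. That was not calculated, and a shift common to all films would not by itself bias that slope.

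**What to change.** 1. For pupil change from baseline, compare the pre-film fixation recording with a second fixation recording after each film's KSS rating. Use the same screen and the same lighting. Because lighting is raised during the wakefulness reset, it must be back at the baseline level before the second film's pre-film recording.
2. Use segments of equal length. If the post-film recording is shorter than 5 min, take a segment of the same length from the baseline.
3. Keep film-period pupil data for contrasts between films, with clip luminance equalised or adjusted for. Luminance regression alone is not a full correction, because it leaves responses to contrast, motion and clip changes.
4. State that film-minus-fixation pupil change is not interpreted as sleepiness.

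The cost is a few minutes of the existing post-condition period of about 10 min, with sensors still on, plus work on clip luminance and wording. The drawback is that the post-film recording reflects the state just after exposure rather than during it. It does, however, fall close in time to the KSS rating with which the pupil data are to be associated.
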